**Study Design**

This will be a retrospective study of the RCGP-RSC cohort. The data available were collected between April 2005 and March 2015 ([name] to confirm). These will be analysed using Read v2 (5-bit) codes to identify patients by the inclusion and exclusion criteria. Laboratory sample data will be taken from the laboratory sample results collected by GP practices.

Inclusion: One or more serum phosphate measurements recorded before a cardiovascular event (primary myocardial infarction; acute coronary syndrome; revascularisation procedure; ischaemic stroke; peripheral vascular disease; vascular dementia), or recorded in patients without any cardiovascular event in the study period. Patients will be aged 18 years and older.

Exclusion: Patients who have already had primary myocardial infarction; acute coronary syndrome or a revascularisation procedure before any serum phosphate measurements have been recorded. Patients with pre-existing ischaemic stroke, peripheral vascular disease or vascular dementia will also be excluded.

Serum phosphate will be a linear variable or analysed further as a categorical variable by range. ‘Time zero’ will refer to the first available serum phosphate measurement of a patient. The time to any outcome measure will be recorded and associations between serum phosphate and outcomes will be analysed by cox-regression.

In patients where more than one serum phosphate measure is available, the mean average of up to the first five measurements from time zero and before any cardiovascular event will be recorded and used in this study.

Importantly, confounding factors for cardiovascular outcomes in all included patients will form part of this study. For each variable, the selected single measurement will be chosen before the outcome measure and as close to time zero as possible, subject to data availability. The exceptions are baseline eGFR and albumin:creatinine ratio – the mean of two measurements in each case will be taken.

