**Confounding variables considered**

Demographics: Age (time zero); gender; ethnicity; body weight and height (to calculate body mass index); BMI; postcode-derived deprivation score (PDDS) (UK Index of Multiple Deprivation 2007); smoking status.

Co-morbidities: Cardiovascular disease (primary myocardial infarction; acute coronary syndrome; revascularisation procedure; ischaemic stroke; peripheral vascular disease; vascular dementia); HbA1c; hypertension (SBP).

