**Statistical analysis**

Numerical data will be refined by excluding values beyond physiological limits. Data will be analysed using the statistical package R, with P values <0.05 being regarded as statistically significant. Expert statistical advice will be sought with the aim of using cox regression models to determine the association between serum phosphate and cardiovascular events, adjusting for the known cardiovascular risk factors. Cox proportional hazards multivariate models will also be constructed to provide a time-event analysis. A backwards stepwise elimination of variables approach will help to refine the model and evaluate the contribution of each variable towards the outcome measures.

Ethical considerations

Approval has been sought from the RCGP for the RSC database to be used for such research projects. Our study is retrospective and observational over anonymised patient data. The study involves no clinical interventions, no patient contact and no breach of confidentiality. The results of the study will be submitted for publication to a peer-reviewed journal.

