**Limitations**

The study population will only include patients that have had sufficient routine blood tests taken. This may introduce bias for increased risk of confounding co-morbidities amongst this group. Serum phosphate levels are influenced acutely and chronically by many factors including disease, exercise and diet - which independently influence cardiovascular risk. We aim to control for cardiovascular risk factors based on the QRISK2 model [6].

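### Hypertension enters the model only as one SBP reading and diabetes only as one HbA1c, with no diagnosis indicator, so confounding by these diagnoses may remain in the phosphate hazard ratio

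*Protocol*

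**What the plan says.** Under Confounding variables considered, the protocol's co-morbidity line consists of prior cardiovascular disease followed by "HbA1c; hypertension (SBP". Hypertension is thus defined as a systolic pressure, and glycaemia is covered by HbA1c alone. Diabetes is not named anywhere in the protocol.

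Study Design sets the measurement rule: "For each variable, the selected single measurement will be chosen before the outcome measure and as close to time zero as possible". It then adds: "The exceptions are baseline eGFR and albumin:creatinine ratio". SBP and HbA1c therefore fall under the single-reading rule.

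The table under Intended output follows this list. It has one systolic pressure row and one HbA1c row, and no row for a hypertension diagnosis, a diabetes diagnosis or treatment for either.

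Two general aims stand beside these lists. Statistical analysis speaks of "adjusting for the known cardiovascular risk factors", and Limitations says "We aim to control for cardiovascular risk factors based on the QRISK2 model". Neither names a diagnosis or treatment variable. Statistical analysis also provides that "A backwards stepwise elimination of variables approach will help to refine the model".

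**The concern.** A marker that treatment lowers does not identify the condition being treated. A patient with long-standing hypertension or diabetes and a normal reading at the chosen date has the same covariate value as a patient who never had the condition, although their cardiovascular risks may differ. The measurement rule does not require the reading to precede time zero, so treatment begun shortly afterwards could also lower the value used.

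The research question is whether phosphate predicts events independently, so the quality of adjustment is central. If a diagnosis missed by the marker is also related to phosphate, part of its effect on events would be credited to phosphate. A large cohort does not help, because a narrow interval shows precision and not freedom from confounding.

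The other listed co-morbidity cannot fill the gap. Patients with pre-existing cardiovascular disease are excluded under Study Design, so that variable is essentially constant at baseline.

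**Working it through.** The protocol gives no effect size, event count or power, so there is no figure to reproduce. The check has a textual part and an illustrative part.

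**1. Text.** Setting the confounder list, the single-reading rule and the output table side by side gives one consistent specification: one SBP, one HbA1c, no diagnosis and no treatment term. The data would allow more, since Study Design says of the records: "These will be analysed using Read v2 (5-bit) codes to identify patients by the inclusion and exclusion criteria". Codes are already used to identify disease.

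**2. Size, by an omitted-variable approximation.** Let p be the share with the condition among patients the marker does not separate, HR_c the condition's hazard ratio at a given marker value, and d the phosphate difference in SD between those with and without the condition. For this purpose d must be the difference that remains after the other covariates. Then

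shift in log HR per SD = ln(HR_c) × p(1−p) × d / (1 + p(1−p)d²).

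All inputs are assumptions; none is in the protocol.

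| Condition (assumed) | d | Shift in log HR | Apparent phosphate HR when the true HR is 1.00 |
|---|---|---|---|
| Hypertension, p = 0.4, HR_c = 1.5 | 0 | 0 | 1.000 |
| | 0.05 | 0.4055 × 0.24 × 0.05 / 1.0006 = 0.0049 | 1.005 |
| | 0.1 | 0.4055 × 0.24 × 0.1 / 1.0024 = 0.0097 | 1.010 |
| | 0.3 | 0.4055 × 0.24 × 0.3 / 1.0216 = 0.0286 | 1.029 |
| Diabetes, p = 0.2, HR_c = 1.7 | 0 | 0 | 1.000 |
| | 0.05 | 0.5306 × 0.16 × 0.05 / 1.0004 = 0.0042 | 1.004 |
| | 0.1 | 0.5306 × 0.16 × 0.1 / 1.0016 = 0.0085 | 1.009 |
| | 0.3 | 0.5306 × 0.16 × 0.3 / 1.0144 = 0.0251 | 1.025 |

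A negative d gives the same log shift with the opposite sign. For hypertension at d = −0.3, exp(−0.0286) = 0.972.

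**3. Does the marker do the work of the diagnosis?** This was simulated with a true phosphate HR of 1.00 and 400,000 patients per scenario. The assumptions were 25% prevalence, 5 years of follow-up, constant hazards, a baseline rate of 0.008 per year and a marker log HR of 0.1 per SD. The marker was raised by 1.5 SD in uncontrolled patients, and 50% or 80% of those with the condition were controlled to a normal marker. The table shows the fall in the phosphate HR when the diagnosis is added to the marker-only model on the same data.

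| d | Condition HR 1.5 (50% / 80% controlled) | Condition HR 2.0 (50% / 80% controlled) |
|---|---|---|
| 0 | 0.000 / 0.001 | 0.000 / 0.002 |
| 0.1 | 0.008 / 0.008 | 0.014 / 0.016 |
| 0.2 | 0.016 / 0.017 | 0.027 / 0.029 |
| 0.3 | 0.024 / 0.024 | 0.042 / 0.044 |

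The clearest example is condition HR 2.0, d = 0.3 and 80% controlled. The phosphate HR was 1.044 unadjusted, 1.041 with the marker only, and 0.997 with marker and diagnosis. Each estimate has a standard error of about 0.007 on the log scale, so the within-dataset differences are more informative than the absolute values. The simulation contains no eGFR, albumin:creatinine ratio, age or BMI, so d again stands for the difference left after them.

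**The case against.** The strongest reply is that much of the likely confounding path is already in the model. Hypertension and diabetes would relate to phosphate largely through kidney function, and the model includes eGFR and albumin:creatinine ratio, each averaged over two measurements. The research question is also stratified by renal function. Age, BMI, albumin, calcium, PTH and vitamin D are in the table too. Bias remains only if the diagnoses still relate to phosphate given all of these, and the protocol does not show that they do. This stands, and it is why the point is worded as confounding that may remain.

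It can also be said that the list is only of variables considered, that expert advice will be sought, and that the general aims already cover known risk factors. This stands only in part. Detailed code lists are normally left to a statistical analysis plan. But the protocol itself fixes the list, the measurement rule and the table rows, and the general aims do not change them.

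A reader might infer more than the protocol supports:

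- **That the residual confounding is certain, or as large as the association sought.** The protocol states no expected hazard ratio, so there is nothing to compare the shift with, and d could be zero or negative.
- **That every treated patient looks healthy.** SBP and HbA1c enter as measurements, so this holds only where the reading has been normalised, and that share is unknown.
- **That HbA1c is recorded mainly in people with diabetes, so the model loses the rest.** The protocol does not say who has HbA1c recorded.

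**Conclusion.** The point holds in a limited form. The protocol equates hypertension with one SBP reading and covers diabetes with one HbA1c. It therefore cannot separate patients with a treated, normalised reading from patients without the condition. Whether this biases the phosphate hazard ratio depends on a conditional association that the protocol does not give, so neither size nor direction can be derived.

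With the two assumed prevalence and hazard ratio pairs and an adjusted phosphate difference of 0 to 0.3 SD, the shift is 0 to about 3% per condition. With a stronger assumed condition HR of 2.0, the simulation reached 0.044. With no remaining phosphate difference there was essentially nothing to remove. This is a weakness in adjustment with a nearly free remedy, not a demonstrated error in the result.

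**What to change.** In Confounding variables considered and in the Intended output table, add diagnosed hypertension and diagnosed diabetes as two yes/no covariates, defined from Read codes dated at or before time zero. Keep SBP and HbA1c as continuous terms beside them. In Statistical analysis, state that these four terms stay in the model regardless of the backward elimination, which could otherwise drop them. Add treatment status only if it is in the extract.

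This also brings the explicit lists into line with the stated aim of adjusting for known cardiovascular risk factors. The cost is two code lists applied to the same extract, two rows in each output table and two extra parameters.

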**Biochemical variables required**

Serum phosphate (as detailed above); vitamin D; parathyroid hormone (PTH); sodium; potassium; cholesterol (total cholesterol, LDL cholesterol, HDL cholesterol); albumin; baseline eGFR and albumin:creatinine ratio.

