**Intended output**

Outcome measure 1, 2 or 3 – each outcome requires its own table

|  | Outcome X | | |
| --- | --- | --- | --- |
| *Variable* | *Hazard ratio* | *95% CI* | *p value* |
| Age |  |  |  |
| Gender |  |  |  |
| Ethnicity |  |  |  |
| BMI |  |  |  |
| PDDS |  |  |  |
| Smoking |  |  |  |
| Syst. BP |  |  |  |
| HbA1c |  |  |  |
| Tot chol |  |  |  |
| LDL |  |  |  |
| HDL |  |  |  |
| Albumin |  |  |  |
| **Phosphate** |  |  |  |
| Calcium |  |  |  |
| Vit D |  |  |  |
| PTH |  |  |  |
| Sodium |  |  |  |
| Potassium |  |  |  |
| Albumin:Cr ratio |  |  |  |
| Baseline eGFR |  |  |  |

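### Total, LDL and HDL cholesterol each get their own row although total cholesterol contains the other two, so wherever all three are in the model the lipid rows and the selection among them mislead

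*Protocol*

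**What the plan says.** Under Biochemical variables required, the protocol lists "cholesterol (total cholesterol, LDL cholesterol, HDL cholesterol" among the laboratory variables. Triglycerides are not listed.

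Under Statistical analysis it plans multivariable Cox models: "Cox proportional hazards multivariate models will also be constructed to provide a time-event analysis". It adds: "A backwards stepwise elimination of variables approach will help to refine the model and evaluate the contribution of each variable towards the outcome measures". The general criterion is "P values <0.05 being regarded as statistically significant". No separate threshold for elimination is given.

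Under Intended output, "each outcome requires its own table", and the table template has separate rows for total cholesterol, LDL and HDL, each with a hazard ratio, 95% CI and p value.

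On where the values come from, Study Design says "Laboratory sample data will be taken from the laboratory sample results collected by GP practices". On timing, the rule that covers the lipids is "the selected single measurement will be chosen before the outcome measure and as close to time zero as possible, subject to data availability". It does not say whether LDL is calculated or directly assayed, or that the three lipids must come from one blood sample.

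The list of variables alone does not put the three lipids into one model. That follows from reading Statistical analysis together with the table template.

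**The concern.** A row in a multivariable table is normally read as the effect of that variable with the others held fixed. Total cholesterol cannot vary with LDL and HDL both held fixed unless the remaining fraction varies. The row labelled total cholesterol therefore describes that fraction. The LDL row describes exchanging LDL for the remainder at constant total, and the HDL row has the same form. Nothing in the table tells the reader this, and triglycerides appear nowhere in it.

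Two things are at stake. The lipid hazard ratios could be published under labels that invite the wrong reading. In addition, the elimination step, which the protocol uses to judge each variable's contribution, could remove LDL or keep it with a protective sign because of how the three quantities add up. If elimination is run separately for each outcome, different lipids could survive in different tables for no substantive reason.

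**Working it through.** The protocol gives no lipid figure, event count or power calculation, so there is no stated number to reproduce. The check has three parts.

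**1. Algebra.** Define the remainder R = TC − LDL − HDL (TC = total cholesterol). Let the log hazard effects per mmol/L be bL (LDL), bH (HDL) and bR (remainder). Substituting for R:

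bL·LDL + bH·HDL + bR·R = bR·TC + (bL − bR)·LDL + (bH − bR)·HDL

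With all three lipids entered, the rows therefore estimate bR for total, bL − bR for LDL and bH − bR for HDL. Illustrative hazard ratios (assumed, with true LDL 1.25 and HDL 0.75):

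| True HR for remainder | Total row | LDL row | HDL row |
|---|---|---|---|
| 1.00 | 1.00 | 1.25/1.00 = 1.25 | 0.75/1.00 = 0.75 |
| 1.25 | 1.25 | 1.25/1.25 = 1.00 | 0.75/1.25 = 0.60 |
| 1.50 | 1.50 | 1.25/1.50 = 0.83 | 0.75/1.50 = 0.50 |

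The LDL and HDL rows match their labels only if the remainder has no effect.

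**2. Collinearity.** Lipids were simulated for 200,000 patients. All inputs are assumptions: LDL SD 0.9, HDL SD 0.35, median triglyceride (TG) 1.3 mmol/L, SD of ln TG 0.3 to 0.6, R = TG/2.2, TG below 4.5. Correlations were −0.1 (LDL with HDL), 0.2 (LDL with ln TG) and −0.4 (HDL with ln TG). An error with SD 0.2 or 0.4 was added to LDL to represent direct assay or a different sample date.

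| LDL value | VIF, total and LDL |
|---|---|
| Calculated, same sample | 8.6 to 31 |
| Error SD 0.2 to 0.4 | 3.8 to 13 |

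The share of LDL variance explained by total and HDL ranged from 0.74 to 0.97. A VIF of 3.8 to 31 multiplies the standard error by √3.8 = 1.9 to √31 = 5.6.

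**3. One simulated Cox analysis.** There were 40,000 patients and 1,875 events, with SD of ln TG 0.5 and no LDL error. True log hazard ratios were LDL 0.25, HDL −0.50, TG 0.10 per mmol/L (so bR = 2.2 × 0.10 = 0.22) and phosphate 0.80. The algebra predicts total 0.22, LDL 0.25 − 0.22 = 0.03 and HDL −0.50 − 0.22 = −0.72. Fitted log hazard ratios (SE):

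| Model | Total | LDL | HDL | Phosphate |
|---|---|---|---|---|
| All three lipids | 0.326 (0.060) | −0.050 (0.069) | −0.775 (0.075) | 0.793 (0.129) |
| LDL + HDL | – | 0.296 (0.026) | −0.581 (0.067) | 0.789 (0.129) |
| Total + HDL | 0.285 (0.023) | – | −0.750 (0.067) | 0.793 (0.129) |

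The fitted values lie within two standard errors of the predictions. The identity can also be checked in the same data. The model with LDL, HDL and TG gave 0.275, −0.449 and 0.148. Then 2.2 × 0.148 = 0.326, 0.275 − 0.326 = −0.051 and −0.449 − 0.326 = −0.775, which match the three-lipid rows to rounding.

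So a variable with a true effect of 0.25 shows −0.050 with z = −0.050/0.069 = −0.72, and elimination at 0.05 would ordinarily consider it for removal. Its standard error is 0.069/0.026 = 2.7 times that in the model without total cholesterol.

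**The case against.** The strongest case against the point has four parts.

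- **The main question concerns phosphate.** Lipids are adjustment variables, and three overlapping lipids adjust at least as fully as any two. This stands: phosphate was 0.793 against 0.789, with the same standard error.
- **Elimination may repair the model by itself.** Dropping LDL leaves total plus HDL, which is the same fit as non-HDL plus HDL because non-HDL is total minus HDL. That is true of the fitted model in this example. The analysis would still report that LDL contributes nothing, against the stated aim. Under other assumed effects, such as the 0.83 row, LDL could be retained with the wrong apparent direction.
- **The exact relation needs calculated LDL from the same sample, which the protocol does not state.** This stands as a limit on size. Direct assay or different dates lower the variance inflation, and R then also absorbs assay and timing differences. Total cholesterol still contains LDL and HDL, so the labels are not restored.
- **Expert statistical advice is to be sought, and the lipid terms may be settled in an analysis plan.** Possibly, but the table template already fixes three rows.

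A reader might also infer that LDL is fully determined by total and HDL, so that the model cannot be fitted. It is not. The triglyceride-related fraction is a third quantity, and with it the lipid design (with intercept) has full rank (4 of 4). Rank falls to 3 of 4 only if LDL were simply total minus HDL.

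**Conclusion.** The point holds as a minor one. Where total, LDL and HDL cholesterol are all in the model, the total row carries the remainder's effect, the LDL and HDL rows are differences from it, and the standard errors for total and LDL are inflated (VIF roughly 4 to 31). Backward elimination can then misstate the contribution of LDL. The algebra needs no assumption about how LDL is obtained. The sizes rest on assumed lipid distributions and effects, and on applying the general 0.05 level to elimination.

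Three wider conclusions might be inferred, and the protocol does not support them:

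- **That every outcome table will be mislabelled.** The protocol does not say whether the tables show the full or the reduced model, so this applies only where all three lipids are retained.
- **That the phosphate result is compromised.** The simulation shows essentially no change.
- **That requiring LDL will lose patients who have no triglyceride result.** This depends on LDL being calculated and on complete-case analysis, neither of which is stated.

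Whether to adjust for lipid-lowering treatment is a separate question and forms no part of this point.

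**What to change.** In Biochemical variables required and in the Intended output template, replace the three lipid rows by one non-redundant set, the same for every outcome. Examples are non-HDL cholesterol (total minus HDL) plus HDL cholesterol, or the total:HDL ratio. In Statistical analysis, state that this set stays in the model together and is not subject to elimination. If LDL is of interest, report it with HDL and without total cholesterol, as a sensitivity analysis at most.

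In the simulated data the first option gives a non-HDL log hazard ratio of 0.285 (SE 0.023). By arithmetic from the total + HDL model, the HDL log hazard ratio is 0.285 − 0.750 = −0.465. Each row then means what its label says, and the phosphate estimate is 0.793, the same as with all three lipids.

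The cost is a change of wording and no new data, since total and HDL are already to be extracted. The downside is that LDL loses its own row in the main tables. The choice among non-redundant sets is a matter of judgement; what matters is that one is fixed before the data are seen.

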**Data source and Sample Size**

RCGP-RSC data will be used for this study. These are from a database of coded primary care data from 135 UK General Practitioner (GP) practices – total population of approximately 1,250,000 patients. A large sample size is necessary for this study due to the variability in serum phosphate concentrations and the duration of the observational period (up to ten years).

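### Measured cholesterol is adjusted for with no record of lipid-lowering treatment, which weakens the lipid adjustment and can pull the LDL and total cholesterol hazard ratios towards 1

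*Protocol*

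**What the plan says.** The Biochemical variables required section lists "cholesterol (total cholesterol, LDL cholesterol, HDL cholesterol" among the laboratory covariates. The table under Intended output gives each of the three its own row for hazard ratio, confidence interval and p value. The Confounding variables considered section holds no lipid variable. Its co-morbidity line gives prior cardiovascular disease and then "HbA1c; hypertension (SBP", with no drug treatment.

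On timing, Study Design says that "the selected single measurement will be chosen before the outcome measure and as close to time zero as possible", with exceptions only for eGFR and albumin:creatinine ratio, which are each the mean of two values. It sets no condition on whether the patient was on treatment when the value was taken, and its exclusions do not mention treatment.

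The stated aim is a Cox model "adjusting for the known cardiovascular risk factors" (Statistical analysis). Limitations adds: "We aim to control for cardiovascular risk factors based on the QRISK2 model". Statistical analysis also says: "A backwards stepwise elimination of variables approach will help to refine the model".

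**The concern.** A cholesterol value measured on treatment does not mean the same as an untreated one. If treatment goes mainly to people judged to be at higher risk, a low LDL marks two different groups: those whose LDL was always low, and those whose LDL was lowered because their risk was high. One LDL coefficient fitted to both is a blend, and it describes neither group well.

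Two things are at stake. First, the lipid hazard ratios are planned outputs, and the protocol wants the contribution of each variable evaluated. A weakened lipid term is also easier for backward elimination to drop. Second, phosphate is the exposure of interest. Any lipid-related or treatment-related risk that the cholesterol terms fail to absorb is left for other covariates to pick up, and phosphate could be one of them.

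In a retrospective extraction, a variable that was not requested is not available at analysis, so the gap is best closed now.

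**Working it through.** The protocol gives no calculated figure on this point, so there is nothing to reproduce. The check has two parts: what the text contains, and how large the effect could be under stated assumptions.

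**Text.** Confounding variables considered, Biochemical variables required, the Intended output table and Limitations contain no medication of any kind. Study Design neither excludes treated patients nor asks for pre-treatment values. The omission is a matter of record.

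**When the LDL coefficient is distorted.** Let k be the hazard of a treated patient relative to an untreated patient with the same measured LDL. If k = 1, measured LDL carries the right risk and nothing is distorted. The problem needs k > 1, either because treatment follows other risk or because it does not undo all past risk. Example of a small k: with an LDL hazard ratio of 1.4 per SD, a fall of 1.2 SD on treatment and a treatment log hazard ratio of -0.25, k = 1.4^1.2 × exp(-0.25) = 1.50 × 0.78 = 1.17.

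**Simulated LDL hazard ratio per SD.** All inputs are assumed; none comes from the protocol.

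| Setting | True | No indicator | With indicator |
|---|---|---|---|
| A. 26% treated, LDL lowered 1.3 SD, k = 1.5-2.0, no renal covariate | 1.30 | 1.17-1.23 | 1.30 |
| B. About 25-28% treated, k = 1.5-2.0, renal covariate in the model | 1.30 | 1.16-1.22 | 1.29 |
| C. 20-40% treated according to LDL and another risk factor (hazard ratio 1.5 per SD) not in the model | 1.40 | 1.13-1.24 | 1.21-1.26 |
| D. 25-40% treated according to LDL alone, k = 1.17 | 1.40 | 1.37-1.41 | not tabulated |

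The attenuation is clear in A to C and almost absent in D, as the argument about k predicts. In C the indicator recovers only part of the loss.

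**Simulated phosphate hazard ratio per SD (true value 1.00).**

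- A, with phosphate tied directly to treatment (odds 1.1-1.5 per SD) and no renal covariate: 1.01-1.04 without the indicator, 1.00 with it.
- B, with phosphate and treatment linked only through renal function and renal function in the model: 0.99 with and without the indicator, differing by about 0.001 at most.
- B, with a further unmeasured treatment indication also related to phosphate (coefficient 0.15-0.30): 1.010-1.023 without the indicator, about 1.005 with it.
- C, with phosphate correlated 0.1-0.3 with both untreated LDL and the omitted risk factor, and no renal covariate: 1.04-1.21 without the indicator, 1.02-1.10 with it. The share of bias removed runs from (1.134 - 1.100)/0.134 = 25% to (1.060 - 1.025)/0.060 = 58%. At correlation 0 there is no bias.
- D: the indicator changes the phosphate hazard ratio by about 0.00-0.01.

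Only the B settings resemble the protocol's model, because eGFR and albumin:creatinine ratio are among its covariates.

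**Would such a bias be significant?** The standard error of a log hazard ratio per SD is roughly 1/√(events). With 10,000 events it is 0.010, and the two-sided 5% threshold is exp(1.96 × 0.010) = 1.020. With 2,000 events it is 0.022, and the threshold is exp(1.96 × 0.0224) = 1.045. A hazard ratio of 1.02 is borderline in the first case and well short in the second. The protocol gives only a source database with a "total population of approximately 1,250,000 patients"; it states no event count, so the question cannot be settled.

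**The case against.** The strongest objection concerns phosphate. A reader might infer that leaving out treatment yields a falsely significant phosphate effect, for instance because poor renal function raises phosphate and also leads to treatment. The documents do not support that. eGFR and albumin:creatinine ratio are both covariates, each averaged over two measurements, and the research question stratifies by renal function. With a renal covariate in the model, that route adds essentially nothing. Any remaining bias needs phosphate to be related to treatment or its indication after age, gender, ethnicity, BMI, deprivation, smoking, blood pressure, HbA1c, lipids and renal function. The protocol gives no figure for that. The rule of "P values <0.05 being regarded as statistically significant" cannot be applied to a hypothetical bias without an event count. This objection stands.

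A reader might also infer that treated patients are modelled as low-risk overall. That is true of the lipid terms only; the other covariates still carry risk. The exclusion of patients with prior cardiovascular disease also removes an obvious group of treated, high-risk patients, which should reduce the problem without ending it.

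Finally, the detail could be left to a statistical analysis plan, to the expert advice that the protocol mentions, or to the reference to QRISK2. This is weaker. The protocol already fixes a named covariate set and a 20-row results table, does not list QRISK2's variables, and names no treatment variable under that aim.

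**Conclusion.** The omission is certain, and its effect on the lipid adjustment is real where treated patients carry excess risk at the same measured LDL. Under assumed values of about a quarter of patients treated and a 1.5- to 2-fold excess, the LDL hazard ratio falls from 1.30 to about 1.16-1.23. If treatment depends on LDL alone and the excess is small, the fall is negligible. Total cholesterol was not simulated; the same reasoning applies because treatment lowers it too.

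Bias in the phosphate hazard ratio is conditional and, on the models closest to the protocol's, small: from none to about 1.02 per SD. Larger figures come from models without a renal covariate. The point is a low-cost improvement to the covariate set. It does not show that the primary estimate is wrong.

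**What to change.** If the dataset holds coded prescriptions:

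1. Add lipid-lowering treatment (yes/no) at time zero to Confounding variables considered, and a row for it to the Intended output table. Where the cholesterol value used has a different date, take treatment status at that date, so that value and status match.
2. Keep the indicator in every model that contains the cholesterol terms, and exempt it from backward elimination.
3. Add a sensitivity analysis restricted to patients untreated at time zero.
4. State in Limitations that the indicator reduces the distortion but may not remove it, since it does not record why or for how long a patient was treated.

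The cost is one code list for the drug class, one more field in the same extraction, one covariate and one extra analysis. The dependence on prescriptions is genuine: Study Design names only Read codes and laboratory results, so availability should be confirmed first. If prescriptions are not held, Limitations should say that lipid values mix treated and untreated patients, and the lipid hazard ratios should be read accordingly.
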